### Data management and confidentiality

All data will be entered electronically by two independent student assistants. Any deviations between the two independent student assistants will be clarified and corrected. Original study forms will be kept on file. All study-related information will be stored in a secure manner and in accessible place. All participant information will be stored in locked in file cabinets in areas with limited access. Participant files will be kept in storage for a period of 10 years after completion of the study. Blood samples will be disposed after analyses.

All laboratory samples, reports, the data collection, the process, and all administrative forms will be identified by a coded ID number, to maintain participant confidentiality. All records that contain names or other personal identifiers, such as locator forms and informed consent forms, will be stored separately from study records, also identified by code numbers. All local databases will be secured with password-protected access systems. Forms, lists, logbooks, appointment books, and any other listings that link participant ID numbers to other identifying information, will be stored in a separate, locked file in an area with limited access. After completion of the study, raw data of all analyses will be archived in an open access repository.

### Sample size calculation

Sample size calculation was done to investigate the effect of exercise-intervention on the primary endpoint (objectively assessed cognitive performance using test battery of the ICCTF), in an analysis of covariance model (ANCOVA) using G*Power 3.1.9.2 software [87]. It was hypothesized that the changes in the test scores in the ICCTF test-battery, from baseline to after completion of the exercise-intervention, differ significantly between the HIIT group and the PCG-training group. Previous studies have shown that regular, low to moderate, exercise exerts rather small beneficial effects on CRCI in breast cancer patients [44–48]. However, pronounced effects of HIIT on fitness, cardiovascular health, fatigue and biomarkers have been reported in cancer patients [55–58]. Changes in these factors are discussed to play a pivotal role in the genesis of CRCI [24]. In accordance with it, we expect more meaningful effects of HIIT on CRCI compared to low to moderate exercise interventions. A medium effect of d = .5 was defined for sample size calculation. Alpha was set at 5%, but Bonferroni corrected due to multiple testing (4 outcome variables), leading to an adjusted alpha of 1.25%. Test power (1-β) was set at 80%. Participants’ test scores at baseline are included as covariate in the model. Required sample size in such an ANCOVA model can be calculated as (1-ρ^2^)*n, with ρ representing the correlation between participants’ baseline and post-treatment outcome-scores and n representing the sample size that would have been required, if a t-test of post-treatment outcome-scores was applied [88]. The correlation between patients’ test scores at baseline and at t_1_ was estimated with ρ = .6. This estimation was based on preliminary results (*N* = 40) of an ongoing trial of our group [89], indicating correlations between baseline and post-intervention measures of the applied tests of .6 and .8. Under the presuppositions made, the sample size calculation showed that 59 patients would be required in each group (*N* = 118). Based on attrition rate reported in existing studies applying HIIT in breast cancer patients during chemotherapy [49, 51] we accounted for 15% drop-out rate, leading to a total sample size of *N* = 136 patients.

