### Study population and recruitment

Participants will be recruited at the Department for Oncology and Hematology of the Clinic Northwest and at the Department for Gynecology at the University Clinic in Frankfurt (Germany). Patients with initial diagnosis of mammary carcinoma stage I-IIIA and scheduled chemotherapy, not fulfilling any of the listed exclusion criteria in Table 2, will be recommended for study participation by the attending physician to the principal investigator. Patients will receive detailed descriptions of the study and will be given sufficient time to ask any questions. Patients will be included in the planned study only after they will give written informed consent. The participants will be included chronologically.

**Table 2 Tab2:** Objectives and hypotheses of the study

Objectives	Hypotheses
Main objective • To evaluate the effects of a HIIT versus placebo, conducted simultaneously with first-line chemotherapy regimen on CRCI, in women with breast cancer	Main hypothesis • In women with breast cancer, the decline in HVLT-R-, TMT-A/B- and COWAT test performance from baseline to completion of the exercise-intervention, is significantly smaller in the HIIT group compared to the control group (hypothesis A)
Secondary objective • To evaluate the effects of a HIIT versus placebo, conducted simultaneously with first-line chemotherapy regimen on self-perceived cognitive performance, in women with breast cancer	Secondary hypotheses • In women with breast cancer, the decline of FACT-COG scores from baseline to completion of the exercise-intervention/to 6-months follow-up^a^_,_ is significantly smaller in the HIIT group compared to the control group (hypothesis B)
• To evaluate the effects of a HIIT versus placebo, conducted simultaneously with first-line chemotherapy regimen on executive functioning subdomain response inhibition, in women with breast cancer	• In women with breast cancer, the decline of INHIB performance from baseline to completion of the exercise-intervention/to 6-months follow up, is significantly smaller in the HIIT group compared to the control group (hypothesis C)

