### Primary endpoint

The primary endpoint of the present study will be the change of test-scores from baseline (t_0_) to after completion of the exercise intervention (t_1_), in the test battery recommended by the International Cancer and Cognition Task Force (ICCTF) to capture CRCI [59]. The ICCTF test battery comprises of the Hopkins Verbal Learning Test – Revised (HVLT-R), Trail-Making-Test A/B (TMT-A/TMT-B) and the Controlled Oral Word Association Test (COWAT).The HVLT-RThe HVLT-R was developed to measure forgetfulness in the domain of verbal memory in individuals at the age of 16 and older [67]. The test includes a list of 12 nouns, which will be read to the participants. Then, the participants will be instructed to repeat as many words from that list as they can remember in any order. This process will be repeated three times. The sum of correct recalled words at all 3 learning trials (“Total-Recall”) has been described as measure of learning efficiency and short-term verbal memory [68] and will be used for analyses. The HVLT-R offers six parallel forms. As recommended for repeated testing, the parallel forms 1, 2 and 4 will be used at t_0_, t_1_ and t_2_ [68]. The order of test forms at the 3 measurement time points will be random but counterbalanced across participants. The HVLT-R shows adequate psychometric properties [69, 70].TMT-A/BThe TMT-A will instruct participants to connect randomly distributed numbers from 1 to 25 as quickly and as correctly as possible, in ascending order. The time participants require for completing TMT part A has been described as a valid measure of selective attention [71] and will be used for analyses in the planned study. TMT-B will instruct participants to connect randomly distributed numbers (1 to 13) and letters (A to L) in ascending order, alternating between numbers and letters as quickly and as correctly as possible. The time participants require for completing TMT part B has been reported as valid measure of executive functioning subdomain set-shifting [71] and will be used for analyses. In the present study, the Langensteinbacher version of the TMT (TMT-L) [72] will be applied. It will be operated via the Wiener Test-System (WTS) (Schuhfried, Vienna, Austria) and adequate psychometric properties have been reported for it [72]. TMT-L parallel versions S1, S2 and S3 will be used in a random order at the 3 measurement time-points, but counterbalanced across participants.COWATThe German version of the COWAT will be used in the present study [73]. Participants will be instructed to name as many words as possible in one min, beginning with a given letter. As recommended in the German test-manual [73], the letters S, P and M will be used at the 3 measurement time points. The order of the letters will be random, but counterbalanced across participants. The number of words participants will produce will be used for analyzation. Adequate psychometric properties for the German version of the COWAT have been reported [73].

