### Statistical analysis

An intention to treat (ITT) analysis will be performed We will also assess the effect of the complete treatment in a per protocol analysis. Separate 2 × 3 mixed ANCOVAs will be conducted to determine the effects of between-subjects factor exercise-intervention, within-subjects factor measurement time-point and their interaction on primary and secondary outcomes. Patients’ baseline scores of each specific parameter will be used as covariate. A significant main effect, of within-subjects factor measurement time-point, will be further investigated through Bonferroni corrected post hoc pairwise comparisons. Simple effects analyses will be conducted to determine potential group differences at each measurement time-point.

ANCOVA assumptions will be explored. In case of violations of normality assumption, appropriate nonparametric procedures will be used. In case of violations of ANCOVA assumptions of homogenous variances or sphericity, F-test will be adjusted. Eta-square values will be reported as effect size estimates for explained variance, and Cohen’s d values will be reported for post hoc pairwise comparisons.

In addition, an exploratory regression-based mediation analysis will be performed for each intervention induced change in biomarker expression. It will be tested if the change in biomarker expression, from baseline to completion of the exercise intervention, partially mediates the effect of the exercise intervention on the change in cognitive performance. The indirect effect, as combined effect of intervention induced change in biomarker and change in biomarker induced change in cognitive performance (i.e. the effect of mediation), will be calculated (product of regression coefficients). The 95% confidence intervals will be created around the indirect effect using bootstrapping [90, 91].

Statistical analysis will be performed by a statistician blinded to treatment groups. Statistical analyses will be conducted using SPSS 25® (IBM®, Armonk, NY, USA). For mediation analyses, the PROCESS custom dialog box (version 3.1, Model 4) for SPSS [91] will be used. A result will be considered significant at *p*-value equal to or less than .5 (in case of primary endpoint this will be adjusted to .0125).

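### Holm's step-down procedure could replace the fixed .0125 threshold for the four primary tests: a cheap gain in power, not the repair of an error

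*Protocol article*

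**What the plan says.** The Primary endpoint section defines the endpoint as the change from baseline to the end of the intervention (t1) in a test battery. Four scores from it are analysed: HVLT-R total recall, TMT-A time, TMT-B time and COWAT word count. The Statistical analysis section plans separate ANCOVAs for the outcomes.

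The Sample size calculation section sets the multiplicity rule: "Alpha was set at 5%, but Bonferroni corrected due to multiple testing (4 outcome variables), leading to an adjusted alpha of 1.25" per cent. The Statistical analysis section repeats it as the significance threshold: "in case of primary endpoint this will be adjusted to .0125". Neither section mentions a step-down or other sequential rule.

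The planning values are also in the Sample size calculation section: "A medium effect of d = .5 was defined for sample size calculation", power of 80%, and "The correlation between patients’ test scores at baseline and at t_1_ was estimated with ρ = .6". They lead to 59 patients per group. For effect reporting, the Statistical analysis section names eta-square and Cohen's d. It states no confidence intervals for the primary tests.

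**The concern.** Fixed Bonferroni holds every test to .0125 whatever the other three show. Once one null hypothesis has been rejected, at most three can still be true, so the remaining tests need not be held to a quarter of 5%. Holm's procedure uses this and Bonferroni does not. For deciding which tests are significant, Bonferroni is therefore never better than Holm and sometimes worse.

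What is at stake is power for claims on individual tests when the intervention affects several of them. The trial considers that plausible: its main hypothesis (Table 2, hypothesis A) names all of the tests. Validity is not at stake, because the stated rule already controls the family-wise error.

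**Working it through.** **Inputs from the protocol article.** Family-wise alpha .05; 4 tests; d = .5; power 80%; ρ = .6; 59 per group. The correlation between the four tests is not given, so it is assumed and varied.

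**1. Reproduce the plan's figures.**
- Per-test alpha: .05 / 4 = .0125.
- Two-sample t-test, two-sided .0125, d = .5, 80% power (noncentral t): n = 91 per group.
- ANCOVA factor, from "Required sample size in such an ANCOVA model can be calculated as (1-ρ^2^)*n": 1 − .6² = .64, and 91 × .64 = 58.24, rounded up to 59. This matches.

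**2. Holm's rule.** Order the p-values from smallest to largest and compare the i-th with .05 / (4 − i + 1). The thresholds are .05/4 = .0125, .05/3 = .0167, .05/2 = .025 and .05/1 = .05. Stop at the first failure. The first step equals the Bonferroni threshold, so two things follow without simulation: every Bonferroni rejection is also a Holm rejection, and the chance of at least one rejection is the same under both.

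**3. Single-test power at each threshold.** The noncentrality is (.5 / √.64) × √(59/2) = .625 × 5.431 = 3.39. By noncentral t, power is 80.3% at .0125, 83.1% at .0167, 86.8% at .025 and 92.0% at .05. The 59 per group remain sufficient, because no test is ever held to a stricter level than .0125.

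**4. Joint comparison by simulation** (200,000 runs, t-based, 59 per group, d = .5 on the affected tests and 0 on the others). Entries are average power per affected test, Bonferroni → Holm.

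| Tests affected | corr. 0 | corr. .3 | corr. .5 | corr. .7 |
|---|---|---|---|---|
| 1 | 80.3 → 80.4% | 80.3 → 80.4% | 80.4 → 80.5% | 80.2 → 80.3% |
| 2 | 80.2 → 82.7% | 80.3 → 82.5% | 80.3 → 82.3% | 80.2 → 82.0% |
| 3 | 80.2 → 85.6% | 80.3 → 85.2% | 80.1 → 84.6% | 80.2 → 84.2% |
| 4 | 80.3 → 89.9% | 80.2 → 88.7% | 80.3 → 87.9% | 80.2 → 87.0% |

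The normal approximation starts slightly higher, at 81.5% per test. With all four affected and correlations of 0 to .6 it rises to 88–91%, a gain of 7 to 9 points. The t-based gain over correlations of 0 to .7 is 6.8 to 9.6 points.

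**5. At least one significant test.** With all four affected, the t-based figures are 99.9%, 98.7%, 96.9% and 94.2% at correlations 0, .3, .5 and .7, the same under both rules.

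**6. Error.** The family-wise error under Holm was at most 4.9% in every configuration with a true null. It can exceed Bonferroni's actual rate: with one test affected and correlation 0, it is 4.7% against 3.7%. Both are within the 5% bound.

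**The case against.** The strongest objection is that nothing here is wrong. The two sections agree on the threshold, the sample size was calculated at it, and each test has about 80% power under the stated assumptions. Choosing Holm could be called a preference. It stands that this is not an error. It does not stand that it is only taste, since Holm loses no rejection, needs no extra patients and keeps the same bound.

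The second objection is that the gain depends on the scenario. This stands fully. With one affected test it is about 0.1 point. With all four affected but only at d = .2 (correlation .3, normal approximation), per-test power goes from 12.7% to 14.6%.

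A reader might go further and infer from hypothesis A that the plan loses a large part of its chance of success. With d = .5 on all four tests and correlation .3, the chance that all four are significant rises from about 53% to 75% under Holm (normal approximation; 50% to 74% t-based). The documents do not support that reading. Hypothesis A names the tests together, that "test performance from baseline to completion of the exercise-intervention, is significantly smaller in the HIIT group compared to the control group (hypothesis A", but no rule says that all four must succeed. If all four were required, no division of alpha would be needed: each could be tested at .05, giving about 76.5% against about 75% with Holm (normal approximation), so Holm would not be the remedy. If one test is enough, Holm leaves the chance of a positive trial unchanged. What remains is a benefit for claims about individual tests.

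Nor is the change entirely without cost. Holm has no simple matching simultaneous intervals. With all four tests affected at d = .5 and correlation .3, about 27% of simulated trials had at least one Holm-significant test whose 98.75% interval included zero.

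**Conclusion.** The point holds as a worthwhile, inexpensive improvement of low severity. The plan's Bonferroni rule is valid and consistent with its sample size, but for deciding which of the four tests are significant, Holm's procedure is at least as good in every case and better when two or more tests respond.

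At 59 per group, d = .5 and ρ = .6, the gain per truly affected test is about 0.1, 2, 4 to 5 and 7 to 9 points for one, two, three and four affected tests. It is zero for the chance of at least one significant result. These sizes rest on the plan's own effect size and baseline correlation, and on an assumed between-test correlation of 0 to .6. The ordering of the two methods rests on neither. The same 5% means the same upper bound, not the same realised error rate.

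**What to change.** Before unblinding, replace the fixed .0125 decision rule in the Statistical analysis section with wording such as: the four group contrasts at t1 (HVLT-R, TMT-A, TMT-B, COWAT) are tested with Holm's step-down procedure at an overall two-sided 5%, and Holm-adjusted p-values are reported. Leave the 1.25% in the Sample size calculation section as the conservative planning basis.

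If intervals are reported for the primary tests, label them as not corresponding to the Holm decisions, since a 98.75% interval can include zero for a Holm-significant test.

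The cost is a sentence or two of text. No patients or assessments are added.

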### Statistical analysis

An intention to treat (ITT) analysis will be performed We will also assess the effect of the complete treatment in a per protocol analysis. Separate 2 × 3 mixed ANCOVAs will be conducted to determine the effects of between-subjects factor exercise-intervention, within-subjects factor measurement time-point and their interaction on primary and secondary outcomes. Patients’ baseline scores of each specific parameter will be used as covariate. A significant main effect, of within-subjects factor measurement time-point, will be further investigated through Bonferroni corrected post hoc pairwise comparisons. Simple effects analyses will be conducted to determine potential group differences at each measurement time-point.

ANCOVA assumptions will be explored. In case of violations of normality assumption, appropriate nonparametric procedures will be used. In case of violations of ANCOVA assumptions of homogenous variances or sphericity, F-test will be adjusted. Eta-square values will be reported as effect size estimates for explained variance, and Cohen’s d values will be reported for post hoc pairwise comparisons.

In addition, an exploratory regression-based mediation analysis will be performed for each intervention induced change in biomarker expression. It will be tested if the change in biomarker expression, from baseline to completion of the exercise intervention, partially mediates the effect of the exercise intervention on the change in cognitive performance. The indirect effect, as combined effect of intervention induced change in biomarker and change in biomarker induced change in cognitive performance (i.e. the effect of mediation), will be calculated (product of regression coefficients). The 95% confidence intervals will be created around the indirect effect using bootstrapping [90, 91].

Statistical analysis will be performed by a statistician blinded to treatment groups. Statistical analyses will be conducted using SPSS 25® (IBM®, Armonk, NY, USA). For mediation analyses, the PROCESS custom dialog box (version 3.1, Model 4) for SPSS [91] will be used. A result will be considered significant at *p*-value equal to or less than .5 (in case of primary endpoint this will be adjusted to .0125).

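### The only model named for the primary endpoint uses, by default, only patients complete at all three visits, so the t1 test can lose randomised patients who miss the 6-month visit

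*Protocol article*

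**What the plan says.** The Primary endpoint section defines the endpoint as the change in each test score "from baseline (t_0_) to after completion of the exercise intervention (t_1"). The visit six months later (t2) serves a secondary hypothesis on sustainability (hypothesis J in the table of objectives and hypotheses).

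The Sample size calculation section sizes the trial for an ANCOVA of the post-treatment score adjusted for baseline, using the baseline-to-t1 correlation. It allows 15% drop-out, "Based on attrition rate reported in existing studies applying HIIT in breast cancer patients during chemotherapy".

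The Statistical analysis section states that "An intention to treat (ITT) analysis will be performed", with a per-protocol analysis besides. It names one model for primary and secondary outcomes alike: "Separate 2 × 3 mixed ANCOVAs will be conducted to determine the effects of between-subjects factor exercise-intervention, within-subjects factor measurement time-point and their interaction". It adds "Patients’ baseline scores of each specific parameter will be used as covariate", "In case of violations of ANCOVA assumptions of homogenous variances or sphericity, F-test will be adjusted" and "Eta-square values will be reported as effect size estimates for explained variance". The software is fixed too: "Statistical analyses will be conducted using SPSS 25". Simple-effects analyses are to compare the groups at each time-point. The section mentions no imputation, no likelihood-based mixed model and no separate t1-only primary model.

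**The concern.** Between- and within-subjects factors, a sphericity check with F adjustment, eta-square and SPSS together describe the classical repeated-measures general linear model. A likelihood-based mixed model with a specified covariance structure has no sphericity step. The classical procedure takes one row per patient and, by default, drops any row with a missing time-point.

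The primary question closes at t1, yet a patient's t1 score would count only if she also came back six months later. Two things are at stake. Usable primary data would be discarded, with a loss of power for which the drop-out allowance makes no provision. The t1 comparison would also be restricted to women selected on an event after randomisation, which is what an ITT analysis is meant to avoid.

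**Working it through.** **Inputs.** From Sample size calculation: d = 0.5; alpha 0.05/4 = 0.0125; power 80%; ρ = 0.6; 59 per group (118 in total); 15% drop-out; 136 in total. Sidedness is not stated; two-sided reproduces the plan's figure. Assumed, because the article gives no figure: loss between t1 and t2 of 5%, 10% or 20% of those seen at t1.

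**Step 1: reproduce the plan's figure.** A two-sample t-test with d = 0.5, two-sided alpha 0.0125 and 80% power needs 91 per group (noncentral t). The ANCOVA factor is 1 − ρ² = 1 − 0.36 = 0.64. Then 91 × 0.64 = 58.24, rounded up to 59 per group, or 118. Inflation: 118 × 1.15 = 135.7, rounded to 136. The plan's figures reproduce. The sizing is therefore for a t1 ANCOVA, with no role for t2.

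**Step 2: what the 15% covers.** It is taken from studies during chemotherapy. In this trial chemotherapy ends at t1 (Data collection and timeline), so the allowance covers loss up to t1. Nothing is added for the next six months.

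**Step 3: patients left.** Seen at t1: 136 × 0.85 = 115.6. Complete at t2 as well: 115.6 × 0.95 = 109.8; × 0.90 = 104.0; × 0.80 = 92.5.

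**Step 4: power of the t1 contrast.** With total N split equally, the noncentrality is [0.5/√(1 − ρ²)] × √(N/4), with N − 3 degrees of freedom. For N = 115.6 and ρ = 0.6 this is (0.5/0.8) × √28.9 = 3.36, against a critical value of 2.54. The same formula at N = 118 gives 80.3%, in line with the planned 80%.

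| Patients used for the t1 test | N | Share of 136 | Power, ρ = 0.6 | Power, ρ = 0.7 | Power, ρ = 0.8 |
|---|---|---|---|---|---|
| All seen at t1 | 115.6 | 85% | 79.3% | 88.8% | 97.3% |
| Also complete at t2, 5% further loss | 109.8 | 81% | 76.7% | 86.8% | 96.4% |
| Also complete at t2, 10% further loss | 104.0 | 76% | 73.9% | 84.6% | 95.4% |
| Also complete at t2, 20% further loss | 92.5 | 68% | 67.5% | 79.1% | 92.5% |

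The columns for ρ = 0.7 and 0.8 are shown because the Sample size calculation reports pilot correlations of 0.6 and 0.8 and plans on the lower.

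The first row is already slightly under 80% at ρ = 0.6, because 118 was multiplied by 1.15 rather than divided by 0.85 (118/0.85 = 138.8, so 139). That is a separate matter from t2. The cost of requiring t2 is the drop from the first row to the rows below it.

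**Step 5: does the layout change this?** Baseline is named as the covariate, and in a 2 × 3 layout it is also one of the three time levels. Under either reading the t2 score has to be present for a patient's row to be complete, so the point holds both ways.

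**The case against.** The article nowhere says that incomplete patients are deleted. Deletion is inferred from the named method and its default behaviour. If scores were imputed first, the same 2 × 3 model could be run on every randomised patient. This is a condensed journal article; a fuller protocol or SAP may say how the ITT set is built, and the promise of ITT beside a separate per-protocol analysis suggests that complete-case analysis was not intended. The simple effects at each time-point, if run as separate t1 ANCOVAs, would also keep patients who miss t2. The t2 loss is an assumption, and ρ = 0.6 is the lower of the two pilot correlations.

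Much of this stands, and it limits the point. A reader might infer that the plan commits itself to a complete-case analysis and so flatly contradicts ITT. The document does not support that: the conflict arises only if nothing is done about missing t2 scores. A reader might also infer that power must fall below 80%. That holds at ρ = 0.6, but at ρ = 0.7 only marginally and only with 20% further loss, and not at ρ = 0.8.

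What does not stand is that this is merely detail left to another document. The article fixes a specific model for the primary endpoint, and that model brings a secondary visit into the primary test. An analysis plan that avoids the loss has to supplement or replace it. Simple effects taken from within the same repeated-measures fit would use the same complete cases, and the text does not say which form is meant.

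**Conclusion.** The concern holds in conditional form. Followed as written and with the software default, the named model drops patients who have t0 and t1 but no t2 from a primary test that ends at t1. This does not fit the stated ITT analysis or the t1 ANCOVA behind the sample size, and the 15% allowance does not cover loss after t1.

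At the planning values, power for the t1 contrast falls from about 79% to about 77%, 74% or 68% for an assumed further loss of 5%, 10% or 20%. With ρ between 0.7 and 0.8 it stays near or above 80%. The result rests on listwise deletion (inferred), on the assumed t2 loss, and on equal loss in the two arms.

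A reader might go further and infer that the t1 estimate will be biased. That is possible if return at six months depends on arm, health or cognition, but nothing in the article shows it or allows its size to be worked out. Severity: should-fix.

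**What to change.** Name one primary analysis that uses every available t1 score. Either of these will do:

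- a baseline-adjusted ANCOVA of the t1 score in all randomised patients with a t1 score, analysed as allocated and tested at 0.0125. This is the model the sample size already assumes; or
- a likelihood-based linear mixed model with t1 and t2 as outcomes, baseline as covariate, and group, visit and their interaction as fixed effects, with the t1 group contrast tested at 0.0125.

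Keep the complete-case 2 × 3 model as a sensitivity or secondary analysis, and state which patients form the ITT set.

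The cost is a few sentences and, for the second option, a different procedure in the same software. No new data or patients are needed. The small downside is that the mixed model assumes data missing at random; the t1 ANCOVA still omits patients without a t1 score, so a sensitivity analysis for missing t1 scores is sensible with either.
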